#### Analysis of heterogeneity of treatment intervention effects

Precision treatment models will be built as in similar studies [88–91]. The models are based on a special case of the super learner (SL) algorithm [92], an ensemble machine learning approach that uses cross-validation (CV) to select a weighted combination of predicted outcome scores across a collection of candidate algorithms that yields an optimal weighted combination according to a pre-specified criterion that performs at least as well as the best component algorithm. The candidate algorithms in SL can either be parametric or flexible machine learning algorithms, making SL less prone to model misspecification than traditional parametric approaches. The guarantee that SL performs at least as well as the best candidate algorithm allows a rich library of parametric and flexible candidate algorithms to be included. In comparison, the conventional approach is to estimate a model with main effects and interactions between prescriptive predictors and dummy variables for treatment indicators [93]. Predicted values based on this model are then used to estimate expected individual-level treatment outcome conditional on prescriptive predictors for each patient in each treatment condition. An estimate of the optimal treatment strategy for patient *p* is then obtained by comparing predicted values of the outcome across all treatment arms. However, the accuracy of this approach requires correct specification of both the (possibly nonlinear) main effects and the (possibly complex nonlinear and higher-order) interaction terms. SL has two advantages over this conventional approach [94]. First, it requires only correct specification of the interactions, not the main effects, as it directly estimates contrasts. Second, SL uses flexible component machine learning algorithms maximizing chances of capturing complex nonlinear and higher-order interactions [92, 95].

The value of guided and unguided iCBT at the individual level will be quantified using an approach roughly equivalent to calculation of NNT in aggregate analyses based on a cross-validated targeted minimum loss-based estimator (CV-TMLE) [96] of the attained improvement of the mean outcome under a treatment selection scheme that always selects the treatment option with the best predicted outcome compared to the mean outcome under balanced randomization, i.e., when *1/3* of students are randomly assigned either guided iCBT, unguided iCBT, or to TAU (which in many cases will result in the student not receiving any treatment). The difference score, sometimes referred to in linear interaction models as the *personalized advantage index* (PAI) [93], quantifies the effect of using a precision treatment assignment rule to determine which patients should receive which treatments. The CV-TMLE estimate of the PAI has minimal bias because it uses CV to separate the estimation of the optimal treatment strategy from the assessment of the estimated strategy’s performance and also by allowing for the incorporation of flexible estimation approaches for the regressions and conditional probabilities needed to define the attained improvement.

### Interim analyses {21b}

Interim analyses will be conducted only to assess adequate randomization (i.e., equal numbers of participants by sex and level of anxiety and depression in each of the three treatment arms) and patterns and predictors of attrition to inform and improve retention strategies. Ongoing data monitoring will also be conducted if requested by the Data Safety Monitoring Board (DSMB).

### Methods for additional analyses (e.g., subgroup analyses) {20b}

As noted above, we will carry out subgroup analyses that evaluate the significance of HTE and attempt to develop an individual PTR to make treatment assignments under balanced allocation that optimize the aggregate remission rate.

### Methods in analysis to handle protocol non-adherence and any statistical methods to handle missing data {20c}

Efforts will be made to minimize loss to follow-up by using contact information obtained at baseline to attempt to contact and encourage non-respondents to complete the follow-up assessment. Mixed mode methods will be used both in contact attempts and to obtain outcome information. We will also attempt to obtain marker information in cases where these participants are unwilling to complete the full follow-up assessment. Reporting of follow-up results will be based on a CONSORT (CONsolidated Standards Of Reporting Trials) checklist and flow diagram [97]. As noted above, we will use IPW to adjust for loss to follow-up [80]. The IPW as of time *t* will be based on the product of these conditional probabilities up through *t*. The treatment-specific mean outcome will be estimated using these weights for the individuals whose outcomes were observed at *t*. Under a coarsening at random assumption, this estimator converges with increasing sample size to the treatment-arm-specific mean outcome that would have been observed had all individuals remained in the study up through *t* [82]. This assumption is closely related to the strong ignorability assumption commonly used in observational studies [83].

### Plans to give access to the full protocol, participant-level data, and statistical code {31c}

Data will become publicly available 6 months after the trials are concluded. First, we will document and make available all imputations, weights, and constructed variables used in our analyses. Second, we will host project webinars to present an overview of the data and answer questions. The webinars will be widely advertised in listservs, including any such sites recommended by NIMH, as well as to National Institute of Health (NIH) training programs. An English version of the webinars will be hosted by the US collaborators. A Spanish version will be hosted by the Mexican collaborators. Third, we will set up and man a project Q&A (question and answer) website in which public users can ask questions and get answers about issues involved in working with the data. Again, the site will be both in English and Spanish. Fourth, we will gather up written versions of all questions asked by public users along with our written response (including any documentation or computer files sent along with these answers) and post these on the website in both English and Spanish as reference documents for future public users.

## Oversight and monitoring

### Composition of the coordinating center and trial steering committee {5d}

The co-PIs who have overall responsibility for coordinating the study will meet periodically with the expert consultants (selected for their experience and research trajectory with clinical trials in general and online interventions in particular), data management staff, the SilverCloud team, the implementation staff, and university liaisons as needed. As described below, there will also be a DSMB.

### Composition of the data monitoring committee, its role, and reporting structure {21a}

The Co-PIs will have overall responsibility for monitoring the integrity of study data and participant safety. In addition, an independent monitoring committee, the DSMB was established to provide oversight for the safe conduct of the study. The DSMB is comprised of four individuals entirely independent of the trial team and with expertise in clinical management of depression, electronic interventions, biostatistics, trial design, ethics, bilingual English-Spanish, and understanding of Latino culture. They will meet quarterly. The DSMB’s main responsibilities include reviewing protocols, consent procedures, and safety plans prior to study initiation, amendments thereafter, and monitoring study progress in terms of recruitment and retention of participants, adverse events, reasons for participant withdrawal, participant privacy, and protocol violations or deviations and will be guided by the NIMH policy governing independent DSMBs [98]. The DSMB will have access to all safety and data quality information collected and will have the authority to stop the study if it raises unacceptable risks to participants. The clinical psychologist supervisor will also oversee the participant safety protocols, the supporter performance, and timely follow-up to any adverse events or serious adverse events (SAEs) over the course of the study, as well as reporting of such events to the Co-PI [name] and the DSMB.

### Adverse event reporting and harms {22}

Regardless of treatment arm, we will monitor the occurrence of two specific SAEs: suicide attempt and unplanned hospitalization from any cause. These will be recorded systematically for all study participants at each outcome assessment (90 days and 12 months). In addition, these SAEs (and any other unexpected adverse event) that are brought to the awareness of the trial team during the trial will be similarly reported and recorded but will not be included in the trial evaluation. Additionally, SAEs may be detected in the guided iCBT by the supporters, which will be reported immediately to the Clinical Supervisor and PI [name]. An initial report of SAEs will be sent to the DSMB within 24 h of the reporting. In all cases of detection of suicide attempts, the student will be immediately told (either by the supporter when detected in the intervention or by automatic message when detected in the survey) that a representative of the student mental health clinic will contact them by the next business day and that they can call the mental health crisis line (which we will provide) prior to that time if they are at imminent risk. All SAEs that are considered study-related will be reported to the NIMH Program Officer within 10 business days and the student will be terminated from the intervention. Students who report suicidal thoughts and behaviors in the baseline survey (used to determine study eligibility) will be given mental health crisis line numbers, flagged, and the university clinical liaison notified to contact that student within 24 h to assess risk and provide help.

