## Data collection and management

### Plans for assessment and collection of outcomes {18a}

The baseline, follow-up, and needs assessment surveys will be self-report scales administered online through the Qualtrics platform. The survey program uses complex skip logic, developed for this study, based on participants’ responses to the questions to reduce respondent burden and increase completeness and accuracy of responses.

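### Deaths and other adverse events that the team learns of outside the two follow-up surveys are left out of the by-arm harms evaluation

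*Protocol article*

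**What the plan says.** All of the reporting rules below come from the protocol article, mostly from Adverse event reporting and harms {22}.

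- **Events named.** The plan states that "we will monitor the occurrence of two specific SAEs: suicide attempt and unplanned hospitalization from any cause". Death is not on this list.
- **Systematic route.** "These will be recorded systematically for all study participants at each outcome assessment (90 days and 12 months"). Plans for assessment and collection of outcomes {18a} gives the mode: "The baseline, follow-up, and needs assessment surveys will be self-report scales administered online through the Qualtrics platform".
- **Other route.** The section then turns to "these SAEs (and any other unexpected adverse event) that are brought to the awareness of the trial team during the trial" and says that they "will be similarly reported and recorded but will not be included in the trial evaluation".
- **Supporters.** The next sentence adds that "SAEs may be detected in the guided iCBT by the supporters". The unguided and treatment-as-usual arms have no supporters.
- **Oversight.** "An initial report of SAEs will be sent to the DSMB within 24 h of the reporting". Under Composition of the data monitoring committee {21a}, "The DSMB will have access to all safety and data quality information collected".

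**The concern.** The plan has two routes by which a harm can become known, and it admits only one of them to the evaluation. That route works only if the student is alive and answers a survey. The most serious event, death, can come only by the route that is shut out. The same holds for a serious event that is on file for a student who does not return to the surveys.

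This matters in this trial for two reasons. Students with elevated depressive or anxious symptoms are recruited, and Eligibility criteria {10} excludes suicide ideation only where there is current intent, so students with ideation but no intent may be randomized. The trial also compares guided iCBT, unguided iCBT and usual care, which often means waiting. Readers will want to know whether serious events differ across these arms, and a harms table that omits events already known to the team cannot fully answer that. If survey retention differs by arm, the omission could also differ by arm.

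**Working it through.** The plan gives no SAE rate, response rate or expected number of deaths, so there is no figure to reproduce. The check is to follow each kind of known event through the stated rules.

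1. **SAE heard of between surveys, then reported by the student at 90 days or 12 months.** It enters through the systematic route. Nothing in the text removes an event from the survey count because the team also heard of it elsewhere. Counted.
2. **Known SAE in a student who misses 90 days but answers at 12 months.** It may be counted if the survey's recall period reaches back far enough. The article does not give the recall period.
3. **Known SAE in a student who answers neither follow-up.** There is no survey report, so the event is known only by the other route. Not counted. The same reasoning applies to an event after 90 days in a student who then does not answer at 12 months.
4. **Known death.** It cannot be self-reported and is not one of the two named SAEs. Not counted, whatever the response rate.
5. **Any other unexpected adverse event.** The systematic route covers two event types only, so this class can enter only by the other route. Not counted, in any arm.

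The number of events lost to the rule is therefore:

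events lost = (events the team learns of outside the surveys) − (those of them also reported in a survey).

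The article gives neither term.

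Next, does any other section bring cases 3 to 5 back into a comparison by arm?

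- **Statistical methods for primary and secondary outcomes {20a}.** Inverse probability weighting uses observed responders to stand for non-responders. It does not insert a known event, and it fails where the event itself causes the non-response. The missing-not-at-random pattern-mixture analysis varies assumptions about unobserved outcomes. It also does not use events that are on file but excluded.
- **Same section, reporting of dropout.** Reasons for missing data are summarized and all patients accounted for. A death could surface there as a reason for loss, but not as a harm.
- **Methods in analysis to handle protocol non-adherence {20c}.** Mixed-mode contact and marker information for students who refuse the full survey may recover some events. SAEs are not named as part of the marker information, and a death stays out of reach of any participant report.
- **Outcomes {12}.** The number of suicide attempts is a secondary outcome, but it comes from the same surveys.

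No section restores the excluded events to a reported comparison.

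**The case against.** The strongest defence is that the rule protects the comparison. Only the guided arm has supporters in weekly contact, so pooling spontaneous reports with survey reports would make guided iCBT look worse simply because more is detected there. The article does not give this reason, but it is a sound one, and it stands as a reason to keep the survey-based comparison as the main one. It justifies separating the events by source. It does not justify leaving out deaths, which depend far less on a supporter's weekly messages than a disclosed attempt does.

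Second, the events are not lost: they are recorded, an initial SAE report goes to the DSMB within 24 h, and the DSMB sees all safety information. This also stands. Board oversight is not, however, a comparison that readers see.

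Third, the term for what the events are kept out of is not defined in this condensed article. It may mean only the formal between-arm comparison, with a fuller listing planned elsewhere. Table layouts are normally left to the analysis plan. The text as written is nevertheless an exclusion rule and not a silence, so it needs a qualification.

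Two stronger readings are tempting and not supported:

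- A reader might infer that a large, calculable share of SAEs is discarded. With an assumed 70% response, the share of SAEs falling in non-responders is 0.3r/(0.7 + 0.3r), where r is their risk relative to responders: 0.30/1.00 = 30% for r = 1 and 0.60/1.30 = 46% for r = 2. The article gives neither the response rate nor r. The figure also measures non-response and not the rule, since many of those events would never become known to anyone on the team.
- A reader might infer that every SAE first learned of outside a survey is thrown out. An event that the student also reports in a later survey is still counted.

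It is also not stated outright that supporter-detected SAEs fall under the exclusion, because they appear in a separate sentence after it. That is the natural reading, but the text leaves it open.

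**Conclusion.** The point holds in a limited form. As written, the plan keeps three classes of known event out of the by-arm harms evaluation: deaths, SAEs in students who answer neither follow-up, and other unexpected adverse events. For deaths and for the third class this follows from the text alone. For the second it depends on the team learning of such events, which the plan itself anticipates.

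The size cannot be given. It is bounded by the events that the team learns of and that no survey also reports, and it may be small. The conclusion rests on reading the excluded scope as the reported evaluation by arm. Efficacy conclusions and DSMB safety monitoring are not affected. The rule should be changed because the omitted events include the gravest ones and would already be on file.

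**What to change.** 1. Keep survey-ascertained suicide attempts and unplanned hospitalizations as the main between-arm comparison of harms, since ascertainment is the same in all arms.
2. Replace the clause that excludes other events from the evaluation with a statement that they are excluded only from that comparison, and say explicitly whether supporter-detected SAEs are among them.
3. Add one table by arm, over all randomized students, of all deaths and all recorded SAEs and unexpected adverse events from any source, with the source of detection shown for each.

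The cost is one sentence and one table from data that the plan already requires to be recorded. The downside is that the added table reflects the extra supporter channel in the guided arm, so it should be labelled descriptive and not used for a formal test between arms.

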### Frequency and plans for auditing trial conduct {23}

Study activities, including those related to consent, randomization, data collection, and intervention, will be monitored on an ongoing basis by the study DSMB. As mentioned above, the DSMB will meet quarterly or more frequently as needed to monitor trial progress and participant safety. As mentioned previously, the DSMB members are independent from investigators and the sponsor.

### Plans for communicating important protocol amendments to relevant parties (e.g., trial participants, ethical committees) {25}

Changes to study protocol will be communicated to the DSMB during quarterly meetings, or through email if required between meetings and as needed to clinical and university partners and participants.

## Dissemination plans {31a}

Study results will be disseminated through webinars and written documents to university administrators and students throughout Latin America, at the participating universities as well as through a consortium of Schools of Psychology in Latin American Universities. We will also prepare scientific reports of the study results for publication in high impact journals.

We will not use any professional writers. At least one individual from each participating university and the central organizing team will be eligible to be an author on future publications if they contribute to conception, design, analysis and/or interpretation of data, and initial drafting or reviewing of drafts.

## Discussion

Both guided and unguided iCBT are promising tools to reduce the personal and societal burdens of mental disorders in general and in the university population of LMICs in particular. The interventions may increase the scalability, affordability, and convenience of treatment delivery. Moreover, the interventions expand the settings to which they can be applied, are flexible, and can use a non-professional workforce [99]. While less is known about relative acceptability of Internet interventions and more traditional treatment delivery methods, the COVID-19 pandemic has been a game changer and made Internet interventions not only more acceptable, but necessary and is likely to remain a cost-effective option once the pandemic is over [100, 101]. This research will provide valuable information to university administrators and government policy makers in the participating LMICs to document the burden of CMDs among university students, the extent of unmet need for treatment of these disorders, the effectiveness of inexpensive-scalable iCBT interventions to treat these disorders, and for whom iCBT is most effective; thus, the more resource-intensive interventions can be saved for those who would not benefit from lesser resource-demanding options. Additionally, this will permit us to build capacity to disseminate the methods used for screening, targeting, and intervention implementation so that they can be used in colleges and universities in LMICs throughout Latin America. Such an effort could have enormous public health implications for the region and serve as a model of evidence-based intervention planning and implementation for other parts of the world.

## Trial status

IRB Approval of Protocol Version 1.0; 6/3/2020. Recruitment began 3/1/2021. Recruitment is tentatively scheduled to be completed 5/30/2024.

## Abbreviations

2SLS: Two-stage least squares
ADHD: Attention deficit hyperactivity disorder
AMDs: Adjusted mean differences
aPRs: Adjusted prevalence ratios
ASRS-V1.1: Adult Self-Report Scale-V1.1
CACE: Complier average causal effect
CBT: Cognitive behavioral therapy
CIDI: Composite International Diagnostic Interview
CIDI-SC: Composite International Diagnostic Interview Screening Scales
CIs: Confidence intervals
CMD: Common mental disorder
CONSORT: CONsolidated Standards Of Reporting Trials
COVID-19: Coronavirus Disease 2019
CSQ-8: Client Satisfaction with Treatment Questionnaire-8
C-SSRS: Columbia Suicidal Severity Rating Scale
CV: Cross-validation
CV-TMLE: Cross-validated targeted minimum loss-based estimator
DSM-5: Diagnostic and Statistical Manual of Mental Disorders, 5th Edition
DSMB: Data Safety Monitoring Board
GAD: Generalized anxiety disorder
GAD-7: Generalized Anxiety Disorder-7 Scale
GLMs: Generalized linear models
HTE: Heterogeneity of treatment effects
iCBT: Internet-delivered cognitive behavioral therapy
ICS: International College Student survey
INPRFM: Instituto Nacional de Psiquiatría Ramón de la Fuente Muñiz [National Institute of Psychiatry Ramón de la Fuente Muñiz]
IPW: Inverse probability weights
IRB: Internal review board
ISI: Insomnia Severity Index
ITT: Intent-to-treat
IV: Instrumental variable
LMIC: Low-middle-income country
MAR: Missing-at-random
MDD: Major depressive disorder
MNAR: Missing-not-at-random
NIH: National Institute of Health
NIMH: National Institute of Mental Health
NNTs: Numbers needed to treat
PAI: Personalized advantage index
PCL-5: PTSD Checklist for DSM-5
PHQ-9: Patient Health Questionnaire-9
PHQ-ADS: Patient Health Questionnaire-Anxiety and Depression Scale
PI: Principal investigator
PRIME-MD PHQ: Primary Care Evaluation of Mental Disorders Patient Health Questionnaire
PTR: Precision treatment rule
PTSD: Post traumatic stress disorder
Q&A: Question and answer
SAE: Serious adverse event
SDS: Sheehan Disability Scales
SITBI: Self-Injurious Thoughts and Behaviors Interview
SL: Super learner
TAU: Treatment as usual
WMH: World Mental Health
WHO: World Health Organization
